#### Supervision records

During the execution of the CCP nurses receive supervision. It focuses on the individual application of the CCP and on the promoting and impeding factors regarding the execution of CC. The supervisions will be audio taped and transcribed verbatim. The records of these supervisions will be examined using content analysis.

#### Data analysis

A distinctive feature of a comparative multiple case study is the analysis of data on three different levels:

Firstly at individual case level, secondly at group level and thirdly at the level of the comparison between the two conditions. At case level the combined quantitative and qualitative data will be used to gain insight in how the application of the CCP in an individual participant has evolved and how this is related to the outcomes. Hence, in first instance a *within case analysis *of the data from different data sources and different perspectives will be made for each individual case. Secondly, within the experimental and the control condition *cross case analyses *will be performed to formulate statements about the observed processes and outcomes per condition. Cases will be subdivided in three categories: (1) a group of cases with positive outcomes; (2) a group of cases with none or minimal changes in outcomes and (3) a group of cases with negative outcomes. Within these three subgroups patient characteristics and the process of application will be compared to explain the different outcomes.

Finally, at an aggregated group level the observed differences in outcomes and process indicators will be examined between the experimental and the control condition (*cross case synthesis*) in order to assess the value of the intervention compared to care as usual and to explain differences in outcomes between the two treatment conditions.

### Qualitative analyses

To describe and understand the process of the application of the CCP versus CAU, the qualitative interviews with patients, their carers and nurses will be analyzed, following the three steps as described above. Beforehand, as preparation for the interviews, the supervision records will be analysed and the quantitative outcomes will be assessed at an individual level.

For the *within case analyses*, the data from the interviews are coded and categorized following the structure as described above. As said, for the *cross case analysis *the participants of both research conditions are divided in three subgroups. Based on the interview data, similarities and differences in the process of the application are described for the three subgroups. The different perspectives of patients, informal caregivers and nurses will be taken into account in this analysis. The degree, to which these perspectives differ from each other, might be indicative for the obtained outcomes. For the *cross case synthesis*, the data from the interviews will be examined to identify group differences between the two research conditions: Which statements do participants make about the underlying principles of the CCP? How do they value these principles? How do they value the outcomes of the CCP resp. CAU?

A content analysis of the supervision records will be performed to identify hampering and fostering characteristics in the process of the application of the CCP from a nursing perspective. For the *within case analysis *this information will be used as a preparation for the interviews. When performing the *cross case analysis and synthesis*, this information exemplifies and partially explains observed outcomes of the application of CCP.

### Quantitative analyses

The used questionnaires provide quantitative data about the outcome indicators from different perspectives. For the *within case analyses *the quantitative data are assessed to describe the individual outcomes. To facilitate the *cross case analysis*, differences in characteristics of the participants within the three subgroups are described. Descriptive analysis of the process forms will give additional information, which will be used for the *cross case analysis and synthesis*.

Statistical analyses will be performed to examine the differences at group level between the experimental and the control condition at the different measurements (*cross case synthesis*). Parametric and non-parametric comparisons of mean scores will be used. These analyses are used to identify preliminary results and to support the qualitative data. These quantitative data combined with the qualitative data provide insights in the value of CC and in the feasibility of the intervention from different perspectives.

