### Participants

#### Patients

Participants are recruited from two comparable community mental health care (CMHC) teams of a large mental health organisation in the Netherlands. One team is indicated as the experimental condition and the other as the control condition.

Both CMHC teams provide long-term outpatient care for patients with various severe mental disorders. Patients that will be included should be between 18 and 65 years of age, have a main diagnosis of borderline or NOS personality disorder (DSM-IV-TR), have a score of 15 or higher on the Borderline Personality Disorder Severity Index (BPDSI, range 0-90) [5,49] and have received psychiatric care for at least two years. Participants are required to speak and read Dutch sufficiently well to fill in the questionnaires.

Participants are excluded when they currently participate in a structured psychotherapeutic program or when it is expected they will participate in such a program within a period of nine months from the start of the study. All participants will be asked to sign for informed consent based on oral and written information about the research project.

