### Selection of patients

The required number of cases for a multiple case study depends upon the heterogeneity among the cases (more heterogeneity requires more cases) and is therefore arbitrary. To take into account the variety in presentation of the disorder and the variety of problems, this study will include at least sixteen patients in each condition. This adds up to 32 cases.

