#### Data collection

There are three measurements in this study: when participants enter the study (T0), after five months (T1) and after nine months (T2). To achieve the formulated objectives of this study, the data collection is divided into two parts. Quantitative data are collected with questionnaires to describe the outcomes of the CC Program in comparison with the CAU (summarized in table 1). Qualitative data, such as interviews, and records of the supervision sessions are used to analyse the implementation process of the application of the CCP in comparison with CAU. Data will be collected among patients, their informal carers and nurses, as mentioned below.

**Table 1 T1:** Summary of the used questionnaires.

	Questionnaires		
Outcome indicator	*Patients*	*Informal caregivers*	*Nurses*
Quality of Life	▪ Manchester Short Appraisal (MANSA)		
Psychopathology	▪ Borderline Personality Disorder Severity Index (BPDSI) ▪ Structured Clinical Interview for DSM-IV Personality Disorders (SCID-II)		
Destructive behaviours	▪ BPDSI ▪ Beck Scale for Suicide Ideation (BSSI) ▪ CAGE questions-adapted to include drugs (CAGE-AID)		▪ Suicide Behaviour Attitude Questionnaire (SBAQ) ▪ Attitudes Towards Deliberate Self-Harm Questionnaire (ADSHQ)
Health care use	▪ Trimbos/iMTA questionnaire for Costs associated with Psychiatric Illness (Tic-P)		▪ process forms
Psychosocial symptoms	▪ Brief Symptom Inventory (BSI)		
Satisfaction	▪ Consumer Quality-index (CQ-index)	▪ CQ-index	
Therapeutic Alliance	▪ *S*cale *t*o *A*sses Therapeutic *R*elationships in Community Mental Health Care (STAR)		▪ STAR
Mastery	▪ Pearlin Mastery Scale (PMS)		
Involvement/social support		▪ Involvement Evaluation Questionnaire (IEQ)	

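### The between-team comparison of mean scores at T1 and T2 has no stated adjustment for T0, so a pre-existing difference between two non-randomised teams is mixed with change under treatment.

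*Protocol article*

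**What the plan says.** Allocation is by team. Under Patients, the article states "Participants are recruited from two comparable community mental health care (CMHC) teams of a large mental health organisation in the Netherlands", and then "One team is indicated as the experimental condition and the other as the control condition". The teams are called comparable, but no matching or balancing of patients is described. The entry criterion on one of the two primary outcomes is a floor: patients must "have a score of 15 or higher on the Borderline Personality Disorder Severity Index (BPDSI, range 0-90".

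Under Selection of patients, "this study will include at least sixteen patients in each condition. This adds up to 32 cases". The number is justified by the variety among cases, not by a power calculation.

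Under Data collection, the schedule is "There are three measurements in this study: when participants enter the study (T0), after five months (T1) and after nine months (T2" in the article's notation.

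The between-group analysis is in Quantitative analyses: "Statistical analyses will be performed to examine the differences at group level between the experimental and the control condition at the different measurements". The method follows: "Parametric and non-parametric comparisons of mean scores will be used". No change score, T0 covariate, group-by-time term or rule for a T0 imbalance is named. The same section gives these tests a preliminary role in support of the qualitative data. The Data analysis section uses the comparison between conditions to assess the worth of the CCP against CAU.

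**The concern.** When groups are not randomised, a difference in means at follow-up has two parts: what the groups brought with them and what happened during treatment. Comparing conditions at each measurement in turn does not separate the two. If the CCP team's caseload has a worse quality of life or a higher BPDSI score at entry, some or all of that difference reappears at T1 and T2. It can look like harm, hide a benefit or, in the other direction, look like benefit.

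At stake is the second objective, the description of preliminary outcomes of CCP against CAU. The Discussion says the results will be used to adapt the program before a randomised trial, so a distorted contrast could misdirect that work. The T0 score is already being collected, and leaving it out of the T1 and T2 comparisons also gives up precision that 32 cases can ill afford to lose.

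**Working it through.** **Inputs from the article.** At least 16 patients per condition, 16 + 16 = 32 (reproduces the stated total); measurements at T0, T1 and T2; one team per condition. There is no powered figure to reproduce.

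**Assumptions, not in the article.** Two-sided 5% test; SD equal to 1 in both teams at both times; T0-to-follow-up correlation r of 0.5 to 0.7; true T0 gap of 0.5 SD, with 0.25 and 0.8 SD as a range; no CCP effect.

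**Step 1: standard error.** SE of a standardised mean difference = √(2/16) = 0.354 SD. For scale, 80% power needs a true effect of (1.960 + 0.842) × 0.354 = 0.99 SD (normal approximation). A gap of 0.5 SD is thus about half the effect that the study could reliably detect.

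**Step 2: what an entry gap does.** Two models bracket the possibilities.
- The gap regresses, so r × gap remains at follow-up: 0.5 × 0.5 = 0.25 SD to 0.7 × 0.5 = 0.35 SD.
- The gap is a stable team difference and persists in full: 0.50 SD.

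Adjustment for T0 (ANCOVA) removes r × gap. It leaves 0 under the first model and (1 − r) × gap = 0.25 to 0.15 SD under the second. A change score removes the whole gap. It leaves 0 under the second model and −(1 − r) × gap = −0.25 to −0.15 SD under the first.

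**Step 3: false-positive rate.** Simulation, 40,000 runs per setting, 16 per group, true gap 0.5 SD, no CCP effect. Cells give bias in SD and rejection rate.

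| r | Gap | Unadjusted follow-up means | ANCOVA on T0 | Change from T0 |
|---|---|---|---|---|
| 0.5 | regresses | 0.25; 10.5% | 0.00; 4.8% | −0.25; 10.4% |
| 0.7 | regresses | 0.35; 16.0% | 0.00; 4.9% | −0.15; 8.3% |
| 0.5 | persists | 0.50; 28.0% | 0.25; 11.7% | 0.00; 5.0% |
| 0.7 | persists | 0.50; 27.9% | 0.15; 8.4% | 0.00; 4.8% |

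Over the same r, the unadjusted test rejects 6 to 8% (regressing) or about 10.5% (persisting) for a gap of 0.25 SD. For a gap of 0.8 SD it rejects 20 to 34%, or about 60%. With no gap, all three analyses stay at about 5%.

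**Step 4: precision.** Adjustment reduces residual variance by r²: 0.5² = 25% to 0.7² = 49%.
- Unadjusted 95% CI half-width: t(30) × 0.354 = 2.042 × 0.354 = 0.72 SD.
- Adjusted half-width: t(29) × 0.354 × √(1 − r²), which is 2.045 × 0.354 × 0.866 = 0.63 SD at r = 0.5 and 2.045 × 0.354 × 0.714 = 0.52 SD at r = 0.7.

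The adjusted figures are for equal observed T0 means. An observed gap of 0.5 SD widens them by a factor of √[(2/16 + 0.25/30)/(2/16)] = 1.03.

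**The case against.** The strongest reply is that this is one short paragraph in a journal article about a study that, by its own account, comes before the question of effectiveness. The tests are preliminary, no significance level or decision threshold is stated, and a fuller analysis plan may exist. That stands as far as severity goes. It does not remove the point, because the article names its method, and that method, followed as written, leaves the entry gap in the T1 and T2 contrasts.

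Three stronger readings are tempting, and the text does not support them.

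- A reader might infer that T0 is ignored and that any entry gap will be presented as a CCP result. T0 is one of the three measurements, so the conditions are compared there too and a gap would be visible. The Data analysis section also sorts cases into groups that include little or no change, which implies use of T0 at case level. Seeing a gap does not take it out of the T1 and T2 differences, however, and nothing says what follows if one is seen.
- A reader might infer that change scores are ruled out. Comparing mean scores does not expressly exclude them; if they are intended, the article should say so.
- A reader might infer that each outcome will get two answers, one parametric and one rank-based. Choosing the test to suit each scale's distribution is at least as natural a reading.

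It is also fair to object that covariate adjustment is no complete cure. If the team difference is stable, ANCOVA on T0 leaves bias, and with one team per condition no T0 model can tell a team effect from a treatment effect.

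**Conclusion.** The point holds in a limited form: the stated comparison of the two teams at T1 and T2 is not adjusted for T0, so pre-existing team differences and change under treatment are mixed in the contrasts used to assess CCP against CAU. For an assumed true gap of 0.5 SD and r of 0.5 to 0.7, the bias is 0.25 to 0.35 SD if the gap regresses and 0.5 SD if it persists, with rejection rates of about 11 to 16% and about 28% at a nominal 5%. These sizes depend on the assumed gap and correlation; the direction of the problem and the gain from adjustment do not. Severity is moderate, given the supportive role of the tests.

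**What to change.** In Quantitative analyses, replace the comparison of mean scores at each measurement with wording to this effect: for each outcome measured at T0, the CCP-minus-CAU difference at T1 and at T2 will be estimated with the T0 score of that outcome as covariate, by ANCOVA or a repeated-measures linear mixed model, and reported as an estimate with its 95% confidence interval. Add a change-from-T0 analysis as a sensitivity analysis, because the two approaches err under opposite assumptions about the gap; agreement between them is reassuring and disagreement should be reported. State as a limitation that, with one team per condition, no adjustment for T0 can separate the team from the treatment.

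The cost is one degree of freedom per model and a little extra analysis. No new data, visits or patients are needed.

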#### Nurses

Ten mental health nurses from the experimental condition and five nurses from the control condition will be included in the study. Participation takes place on a voluntary basis. Nurses who participate in the experimental condition will receive a three-days training in providing the Collaborative Care Program. Nurses in the control condition will offer Care as Usual.

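### With 16 patients per condition, the planned comparisons of mean scores should be reported as baseline-adjusted differences with 95% confidence intervals, because as tests they would settle little

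*Protocol article*

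**What the plan says.** All references are to the Protocol article.

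- **Method (Quantitative analyses).** Statistical analyses examine "differences at group level between the experimental and the control condition at the different measurements", and "Parametric and non-parametric comparisons of mean scores will be used". The same section treats the process forms separately, with descriptive analysis only.
- **Stated role (Quantitative analyses).** "These analyses are used to identify preliminary results and to support the qualitative data".
- **Use (Data analysis).** The between-condition step serves to judge what the intervention is worth relative to usual care and to explain differences in outcome.
- **Number of patients (Selection of patients).** The required number "depends upon the heterogeneity among the cases (more heterogeneity requires more cases) and is therefore arbitrary"; on that basis "this study will include at least sixteen patients in each condition", 32 in all.
- **Nurses.** "Ten mental health nurses from the experimental condition and five nurses from the control condition will be included in the study".
- **Allocation (Patients).** "One team is indicated as the experimental condition and the other as the control condition".
- **Timing (Data collection).** Three measurements: entry (T0), five months (T1) and nine months (T2).
- **Hierarchy.** Quality of life (MANSA) and the BPDSI are primary outcome indicators. All other scales are secondary or process indicators.

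**The concern.** The number of patients was set so that the cases vary enough for a case study. The same patients then carry group comparisons on many scales at several times. If these are read as tests, a non-significant result is likely even where the program has a useful effect, and some positive results will arise by chance. Both feed the judgement on the program's value and, according to the Discussion, its adaptation before a randomised trial. A component could be dropped or kept because a scale happened to fall on one side of a threshold.

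Two features of the stated method add to this. Comparing groups at each measurement, as written, makes no use of the T0 score, although the two teams are not randomised and may differ at entry. And the usual rank tests compare distributions, not mean scores, so the sentence puts two different questions under one label.

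**Working it through.** **The plan's own figure.** There is no power calculation to reproduce. The only arithmetic is 2 × 16 = 32, which is correct.

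**Inputs from the article.** At least 16 patients per condition; ten and five nurses; follow-up at T1 and T2.

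**Assumed, because the article gives none.** Two-sided 5% per comparison; true differences of 0.3 to 1.0 SD; 12 completers per group as a dropout scenario.

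**Step 1: power.** For two means, the noncentral t has n1 + n2 − 2 degrees of freedom and noncentrality d × √(n1·n2/(n1+n2)). At d = 0.5 the noncentrality is 0.5 × √(256/32) = 1.41 for 16 v 16, and 0.5 × √(50/15) = 0.91 for 10 v 5.

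| Groups | 0.3 SD | 0.5 SD | 0.8 SD | 1.0 SD | 80% power at |
|---|---|---|---|---|---|
| 16 v 16 | 13% | 28% | 59% | 78% | 1.02 SD |
| 12 v 12 | 11% | 22% | 47% | 65% | 1.20 SD |
| 10 v 5 | 8% | 14% | 27% | 39% | 1.66 SD |

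For 80% power at 0.5 SD, about 63 patients per group would be needed (normal approximation). The 10 v 5 row applies to the nurses' attitude scales. It applies to their STAR score only if each nurse gives one score, which the article does not say.

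**Step 2: number of comparisons (my count).**

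- Patients, 11: MANSA, BPDSI total, the two BPDSI subscale scores named under Destructive behaviours, BSSI, CAGE-AID, TiC-P, BSI, CQ-index, STAR, mastery.
- Carers, 2: CQ-index, IEQ.
- Nurses, 5: STAR, three SBAQ subscales, ADSHQ.

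That gives 11 + 2 + 5 = 18. The SCID-II (baseline) and the process forms (descriptive) are left out. T0 comparisons show comparability rather than effect, so the count is 18 × 2 = 36.

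**Step 3: chance positives if nothing differs.**

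- Expected number: 36 × 0.05 = 1.8.
- At least one, if independent: 1 − 0.95^36 = 84%.
- At least one, with correlation 0.5 between all scores (simulation, 4,000 runs, 16 v 16 throughout): about 56%.
- The two primary scales at T1 and T2 only: 4 × 0.05 = 0.2 expected; 1 − 0.95^4 = 18.5% if independent.

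**Step 4: what share of positives would be chance.** With a share π of scores truly differing, the false share is (1 − π)·0.05 / [(1 − π)·0.05 + π·power]. At 0.5 SD (power 0.278):

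- π = 10%: 0.045/(0.045 + 0.0278) = 62%
- π = 25%: 0.0375/(0.0375 + 0.0695) = 35%
- π = 50%: 0.025/(0.025 + 0.139) = 15%

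The share passes one half only when π is below 0.05/(0.05 + 0.278), about 15%. The article gives nothing from which π could be judged.

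**Step 5: what an interval would show.** The unadjusted 95% half-width is t(0.975, df) × √(1/n1 + 1/n2) in SD units.

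- 16 v 16: 2.042 × 0.354 = 0.72 SD
- 12 v 12: 2.074 × 0.408 = 0.85 SD
- 10 v 5: 2.160 × 0.548 = 1.18 SD

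Adjustment for the T0 score multiplies this by roughly √(1 − r²), where r is the unknown correlation between T0 and follow-up. At 16 v 16 that gives 0.72 × 0.95 = 0.69 SD at r = 0.3 and 0.72 × 0.87 = 0.63 SD at r = 0.5, before any loss from imbalance at T0.

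**The case against.** The strongest reply is that the article never commits to significance testing. The section gives no alpha, p-value or decision rule, and a comparison of means can be reported as a difference with an interval. The article is condensed, so the choice of test, the lead contrast and the handling of multiplicity may stand in a fuller plan. It names two primary scales, calls the results preliminary and supportive, makes the group comparison the last of three levels of analysis, and states that the study comes before any question of effectiveness.

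Much of this stands. The absence of a lead contrast or of a rule for choosing between tests is not held against the article. Testing remains an inference, but it is the ordinary reading: the section sets statistical analyses apart from descriptive ones, and the parametric/non-parametric distinction belongs to inference. The preliminary label limits the harm to over-reading. It does not remove it, because the Data analysis section still uses the group comparison to assess value.

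Three stronger readings are tempting and are not supported:

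- *Most positive results would be chance.* Step 4 shows that this depends on how many scores truly differ, which is unknown.
- *A false positive somewhere is nearly certain.* The 84% needs independence, yet the scores include a total with its own subscales, measured twice in the same people. The counts of 18 and 36 are also mine, since the article does not say that every scale and subscale will be compared.
- *Using both kinds of test seriously inflates error.* In 20,000 simulated comparisons at 16 v 16, taking either test as positive gave 5.7% on normal and 5.9% on lognormal data. That is about one point above 5%, and it assumes the better result is always picked.

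**Conclusion.** The point holds in a limited form, minor to moderate. If the comparisons are read as two-sided 5% tests, a non-significant result on a patient scale is uninformative for differences of moderate size: power is 28% at 0.5 SD with all 16 per condition, and 22% if 12 complete. Scores resting on ten against five nurses are weaker still, at 14%. Over some 36 comparisons, one or two chance positives are to be expected if nothing differs, and what share of the positives seen would be chance cannot be known. The reference to mean scores is also inexact for rank tests.

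These figures rest on the assumed 5% level, on differences in SD units, and on independent patients within each condition. A reader might infer that the quantitative part of the study is worthless or misleading; the article's stated limits do not support that. Nor would estimation solve everything: with one team per condition, a difference between teams biases an estimate just as it biases a test.

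**What to change.** Replace the quoted sentence with wording to this effect:

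> Between-condition differences at T1 and T2, adjusted for the T0 score of the same scale, will be reported with 95% confidence intervals, MANSA and BPDSI total first. Any p-values are descriptive. Rank-based methods serve only as a labelled sensitivity analysis for skewed scores. An interval that includes zero is not evidence of no effect. Differences between the two teams cannot be separated from the effect of the intervention.

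Report the SDs and T0–T2 correlations of the main scales for planning the randomised trial. A nurse-level intraclass correlation is not worth adding: 16/10 = 1.6 and 16/5 = 3.2 patients per nurse would leave it too imprecise to plan on.

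The cost is wording only. T0 scores are already to be collected, and no patient, visit or questionnaire is added. The investigators give up significance claims on the secondary scales, and the intervals will be wide (about ±0.72 SD unadjusted at 16 v 16), which shows readers how much the data can bear.
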